### Data Analysis

Preliminary data analysis is scheduled for early June 2024, while the final results will be available at the end of the study (second half of 2024). The publication of the results will take place within 1 year after the conclusion of the study.

#### Quantitative Analysis

Statistical data processing will be conducted using the software R (version 4.0.0; R Foundation for Statistical Computing), SPSS Statistics (IBM Corp), and Stata17 (StataCorp LLC).

Categorical variables will be summarized by absolute and percentage frequency distributions and quantitative variables of appropriate centrality and variability indexes.

Descriptive analyses will be calculated both for psychological variables (QoL, anxiety, stress, depression, distress, the impact of external events, mindfulness, positive and negative affect, and emotional regulation) and usability (UX) and user involvement (UE) variables. These analyses will be performed on the variables analyzed at the beginning, during, and at the end of the interaction with Maia.

The relationships between variables will be analyzed mainly through ad hoc statistical tests, such as the chi-square test, Fisher exact test, 2-tailed *t* test for paired data or Wilcoxon nonparametric tests, and the sign test (based on an assessment of compliance with assumptions), to understand the differences between the beginning and the end of the course in the same study sample with respect to the variables under investigation.

Furthermore, univariate logistic models or multinomial regression models will be presented. Finally, to consider possible confounding factors, multiple regression models will be proposed, where the effects of the explanatory variables on the outcome variables will be adjusted for possible confounders.

For each analysis, statistical significance will be set at a *P* value of ≤.05.

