### Study Outcomes

#### Primary Outcome

The primary outcomes are UX and UE. They will be assessed using 2 questionnaires, namely, the Mobile Application Rating Scale (MARS) [19] and the User Engagement Scale–Short Form (UES-SF) [20], which will be administered at different time slots throughout the study, in particular, at the end of week 4 and at the end of the study (ie, week 8).

The end points that will be measured are as follows: a score of the individual items of the questionnaires (MARS and UES-SF); the average score of the questionnaires; and the difference between the average score values of the individual questionnaires at different survey times.

The evaluation of the experience of using the app and the virtual coach (Maia) and the use of the intervention itself will also be assessed through semistructured interviews, conducted 2 months after childbirth. In this case, qualitative data will be collected to enrich the information related to the primary outcome.

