#### Secondary Outcome

The variable expressing the “psychological well-being” outcome will be assessed by administering self-report questionnaires at the beginning (ie, week 1) and end (ie, week 8) of the psychoeducational course (refer to Table 1 for a detailed overview of the questionnaire adopted). The end points that will be measured are as follows: a score of the individual items of the questionnaires; the average score of the questionnaires; and the difference between the average score values of the individual questionnaires in the 2 survey times.

**Table 1 table1:** Summary of the questionnaires administered and their timing.

At the beginning of the study (week 1)	At the end of week 4	At the end of the study (week 8)	Follow-up (2 months after birth)
SF-12 v1^a^	N/A^b^	SF-12 v1	Qualitative interview
DASS-21^c^	N/A	DASS-21	N/A
IES-R^d^	N/A	IES-R	N/A
FFMQ^e^	N/A	FFMQ	N/A
PANAS-SF^f^	N/A	PANAS-SF	N/A
ERQ^g^	N/A	ERQ	N/A
N/A	MARS^h^	MARS	N/A
N/A	UES-SF^i^	UES-SF	N/A

^a^SF-12 v1: Short Form–12 Health Survey Version 1.

^b^N/A: not applicable.

^c^DASS−21: Depression Anxiety Stress Scales–21.

^d^IES-R: Impact Event Scale–Revised.

^e^FFMQ: Five Facet Mindfulness Questionnaire.

^f^PANAS-SF: Positive and Negative Affect Schedule–Short Form.

^g^ERQ: Emotion Regulation Questionnaire.

^h^MARS: Mobile Application Rating Scale.

^i^UES-SF: User Engagement Scale–Short Form.

The mindfulness-based childbirth and parenting protocol is aimed at creating a connection between expectant mothers and their bodies and fetuses. The literature highlights the growing interest in mindfulness-based interventions [21] due to their consistent effects, including reduced depressive [22], anxiety [23], and stress symptoms [24] as well as enhanced emotional regulation [25] and sleep quality [26].

Therefore, we intend to incorporate variables such as maternal stress levels, frequency of mindfulness practice, and gestational age as predictors. Particularly, we will explore stress and anxiety (Impact Event Scale–Revised and Short Form–12 Health Survey, Version 1), depression (Depression Anxiety Stress Scales–21), emotion regulation (Positive and Negative Affect Schedule–Short-Form and Emotion Regulation Questionnaire), and mindfulness level (Five Facet Mindfulness Questionnaire).

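### Chi-square and Fisher exact tests are listed for beginning-versus-end differences in the same women; for dichotomous or categorical items they ignore the pairing or test association instead of change

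*Protocol article*

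**What the plan says.** In the protocol article, the Quantitative Analysis section puts five kinds of test in one sentence. It names "ad hoc statistical tests, such as the chi-square test, Fisher exact test", then the paired t test, Wilcoxon tests and the sign test. The choice among them is "based on an assessment of compliance with assumptions". The sentence opens by speaking of relationships between variables, but the purpose it states is "to understand the differences between the beginning and the end of the course in the same study sample". No test designed for paired categorical data, such as McNemar or Stuart-Maxwell, is named. The same section sets significance at P ≤ .05 for each analysis.

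The end points to which these tests could apply are given under Study Outcomes. For the secondary outcome they are "a score of the individual items of the questionnaires; the average score of the questionnaires; and the difference between the average score values" at the two survey times. The primary outcome is built in the same way: "a score of the individual items of the questionnaires (MARS and UES-SF); the average score of the questionnaires". Individual items are therefore end points in their own right. The Data Collection section says that SF-12 items are partly Likert and partly dichotomous, and the SF-12 is given at weeks 1 and 8.

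**The concern.** Pearson chi-square and Fisher exact compare independent groups. Here the same woman answers at the beginning and at the end, so the two observations are dependent by design. Checking assumptions cannot remove that; it can only lead the analyst to a different test.

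There are two ways to run these tests on before-after data, and neither answers the question asked:

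- **Stacked.** The rows are the two time points and the columns the answer. Forty women are then treated as 80 independent subjects. With a positive within-woman correlation the standard error is too large, so the test is conservative and loses power.
- **Cross-tabulated.** The rows are the answer before and the columns the answer after. The test then asks whether the two answers are associated. They nearly always are, whether or not anything changed.

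At stake are the item-level P values for before-after change in dichotomous or categorically treated items. They could hide a real change or, in the second layout, report one that did not occur.

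**Working it through.** **Number of pairs.** The Sample Size section needs 41 women for parametric tests and allows 20% dropout: 41 × 1.2 = 49.2, rounded up to 50, which is the article's figure. With 20% lost, 50 × 0.8 = 40 pairs remain.

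**Other inputs.** α = .05 (Quantitative Analysis). The article gives no item proportions or before-after correlation. I assume 30% at both times for no change, 40% to 20% for a change, and a latent normal correlation of 0.3, 0.5 or 0.7.

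**Why the stacked test is conservative.** The true variance of the difference between two paired proportions is [p₁(1−p₁) + p₂(1−p₂) − 2φ√(p₁(1−p₁)p₂(1−p₂))]/n. Chi-square omits the φ term. With p₁ = p₂ the true variance is (1−φ) times the one used, so the size is about 2Φ(−1.96/√(1−φ)). At 30%, the three latent correlations give φ = 0.18, 0.32 and 0.48:

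- 0.3: 1.96/√0.82 = 2.17, size about 3.0%
- 0.5: 1.96/√0.68 = 2.37, size about 1.8%
- 0.7: 1.96/√0.52 = 2.72, size about 0.7%

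**Rejection rates.** I enumerated all 2×2 before-after tables with 40 women and added up their probabilities. Simulation of the same scenarios agrees to within about one percentage point.

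| Test at α = .05 | 0.3 | 0.5 | 0.7 |
|---|---|---|---|
| *No change, 30% to 30%* | | | |
| Chi-square, stacked | 3.0% | 1.8% | 0.7% |
| Fisher, stacked | 1.6% | 0.8% | 0.3% |
| McNemar, asymptotic | 4.6% | 4.3% | 4.3% |
| Chi-square, cross-table | 22% | 52% | 86% |
| *Change, 40% to 20%* | | | |
| Chi-square, stacked | 50% | 50% | 49% |
| Fisher, stacked | 40% | 39% | 38% |
| McNemar, asymptotic | 56% | 62% | 73% |
| McNemar, exact | 47% | 53% | 63% |

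**Two invented tables that can be checked by hand.**

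1. *A change.* Of 40 women, 6 endorse an item both times, 10 only before, 2 only after and 22 never: 16 before, 8 after. Stacked chi-square: pooled proportion 24/80 = 0.30, standard error √(2 × 0.30 × 0.70/40) = 0.1025, z = 0.20/0.1025 = 1.95, P = .051. McNemar: (10−2)²/(10+2) = 5.33, P = .021. Exact McNemar: 2 × (1+12+66)/4096 = .039.
2. *No change.* Here 8 endorse both times, 4 only before, 4 only after and 24 never: 12 before, 12 after. McNemar is 0. Chi-square on the cross-table is 40 × (8×24 − 4×4)²/(12×28×12×28) = 10.98, P < .001. It detects that women answer consistently, which says nothing about change.

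**The case against.** The strongest reply is that this is loose wording in a condensed article. The sentence begins with relationships between variables, for which chi-square and Fisher are ordinary tools, and the study collects categorical sociodemographic variables. The same list holds valid paired tests. Paired t and Wilcoxon serve the average scores; Wilcoxon or the sign test serves Likert items. On a binary item the sign test applied to the discordant pairs is the exact McNemar test, so a valid option is already present. The analysis is described in the Abstract as mainly descriptive, before-after well-being is secondary, and the Limitations leave effectiveness to a later randomised trial.

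Most of this stands, and it limits the point. It does not remove it: the stated purpose of the list is change in the same women, and nothing reserves chi-square or Fisher for other questions or gives the sign test the binary items.

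Three stronger readings are tempting, and the article does not support them.

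- A reader might infer that logistic or multinomial models will be fitted to continuous scores after cutting them into categories. The article says only that "univariate logistic models or multinomial regression models will be presented". It names no outcome and no cut-point, and it separately proposes multiple regression. Dichotomous items exist to which a logistic model could apply.
- A reader might infer that all before-after comparisons lose power. Only those in which chi-square or Fisher is actually used do.
- A reader might infer that these tests are always far too conservative. For stacked chi-square, a size below 1% appears only at the highest correlation assumed; at 0.3 it is 3%, and exact McNemar then has slightly less power than chi-square (47% against 50%). In the cross-table layout the error runs the other way.

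**Conclusion.** The point holds for dichotomous items and for any item treated as categorical. The plan assigns tests for independent observations to a paired comparison, and an assumption check cannot cure that. Used on stacked data, chi-square has a true size of about 3% to 1% instead of 5%. Its power for a 40% to 20% change is about 50%, which is 6 to 23 percentage points below asymptotic McNemar; against exact McNemar the difference runs from 3 points in chi-square's favour to 13 or 14 points against it. Used on the cross-table and read as change, it gives a false finding in 22% to 86% of samples.

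These figures rest on 40 completers, the assumed proportions and an assumed latent correlation of 0.3 to 0.7. They show direction and rough size and are not predictions for this study. The average-score end points are not affected. Since before-after well-being is a secondary outcome in a mainly descriptive study, severity is minor to moderate.

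**What to change.** In the Quantitative Analysis section, split the sentence by type of variable and question:

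- scores and ordinal items, before versus after: paired t, Wilcoxon signed-rank or sign test, as already listed;
- binary items, before versus after: McNemar, stating whether the asymptotic or the exact version is used;
- items with more than two categories treated as nominal, before versus after: Stuart-Maxwell test of marginal homogeneity;
- chi-square and Fisher exact: only for associations between different variables or comparisons between subgroups of women.

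The cost is wording only. No extra data or women are needed, and the tests are available in the software that the article names.

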### Sample Size

This research project is designed as a proof-of-concept study, where a small sample is sufficient to achieve the intended aims. It was calculated that if nonparametric statistics are conducted (assuming the distribution is not normal), the sample should consist of 24 pregnant women with Bonferroni correction (Cronbach α=.025). The sample size and power for nonparametric tests (Kruskal-Wallis test and Wilcoxon post hoc test) c according to Noether [18]. If parametric statistics are conducted (assuming the normal distribution), the sample must instead consist of 41 pregnant women with Bonferroni correction (α=.025). Thus, with a power level set at 0.80, a significance level of .025, and factoring in a 20% potential dropout rate, we estimated that recruiting 50 women would be necessary to conduct the study.

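### The sample size rests on a Bonferroni-corrected significance level of .025 for two unnamed comparisons, but the analysis section tests every comparison at .05, so the stated error control is not applied

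*Protocol article*

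**What the plan says.** The Sample Size section gives two completer numbers, each with a Bonferroni correction to .025: 24 women for nonparametric statistics and 41 for parametric statistics. It concludes, "with a power level set at 0.80, a significance level of .025, and factoring in a 20% potential dropout rate", that "we estimated that recruiting 50 women would be necessary to conduct the study". It does not say which comparisons share the correction.

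The Quantitative Analysis section lists the tests for beginning-to-end change, among them the "2-tailed *t* test for paired data or Wilcoxon nonparametric tests, and the sign test", and adds regression models. It closes with "For each analysis, statistical significance will be set at a *P* value of ≤.05". No correction appears there.

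The Secondary Outcome section and Table 1 schedule six well-being questionnaires at week 1 and week 8: SF-12, DASS-21, IES-R, FFMQ, PANAS-SF and ERQ. The end points listed are "a score of the individual items of the questionnaires; the average score of the questionnaires", followed by the change in the average questionnaire scores between the two survey times. The Primary Outcome section uses two other questionnaires, MARS and UES-SF, at weeks 4 and 8.

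**The concern.** A significance level used to size a study should be the one used to analyse it. Here the design level is half the analysis level, and the halving is expressly a multiplicity correction. Read as written, the correction affects how many women are recruited and then has no effect on which results are called significant.

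This bears on the interpretation of the results. The article expects improvement in well-being, quality of life, emotional regulation and positive affect, and makes possible later roll-out depend on positive results, after an evaluation of effectiveness. It does not say which score decides whether results are positive. With six questionnaires each tested at .05, a single small P value could be presented as the expected improvement, while the Sample Size section gives the impression that the error rate had been controlled.

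**Working it through.** **Inputs from the protocol article.** Sample Size: level .025, power 0.80, dropout 20%, 41 completers (parametric), 50 recruited. Quantitative Analysis: .05 for each analysis, two-tailed paired t test. Secondary Outcome and Table 1: six questionnaires measured before and after.

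**Assumptions, not in the documents.** Standardized paired difference (mean change divided by the SD of the changes) of 0.5, with a range shown. Correlations between scores of 0.3 to 0.7, for illustration.

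**1. The plan's own figures.**
- Bonferroni: .05/2 = .025, hence two comparisons.
- Recruitment: 41 × 1.2 = 49.2, rounded up to 50, which is the stated figure. Dividing instead gives 41/0.8 = 51.25, or 52.
- Completers: a paired t test (noncentral t) at two-sided .025 and power 0.80 needs 62, 41 and 29 women at differences of 0.4, 0.5 and 0.6. The stated 41 is reproduced at 0.5. It is also reproduced at 0.45 if the test is one-sided at .025; the section does not state sidedness.
- The nonparametric 24 cannot be checked, because no effect is given for it.

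**2. Effect of the mismatch for two tests.** With no true change and independent tests, the chance of at least one false positive is 1 − (1 − α)^k.
- k = 2, α = .025: 1 − 0.975² = 4.9%.
- k = 2, α = .05: 1 − 0.95² = 9.8%.

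**3. Six pre-post questionnaire scores, one per questionnaire.**

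| Case | Any false positive at .05 | False improvement only, at .05 | Any false positive at .025 |
|---|---|---|---|
| Independent | 1 − 0.95⁶ = 26.5% | 1 − 0.975⁶ = 14.1% | 1 − 0.975⁶ = 14.1% |
| Correlation 0.3 | 24% | 12% | 13% |
| Correlation 0.5 | 21% | 10% | 11% |
| Correlation 0.7 | 16% | 8% | 9% |

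The correlated rows come from simulating six equally correlated normal test statistics. The third column uses .025 per test because a two-sided .05 test puts half its error in the direction of improvement.

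**4. Cost of testing all six formally.** The strictest Holm step is .05/6 = .0083. At a difference of 0.5, power at that step is 65% with 40 women (50 less 20%) and 66% with 41. With 40 women it is 41% at a difference of 0.4, 53% at 0.45 and 84% at 0.6. Reaching 80% at a difference of 0.5 takes 52 completers.

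**The case against.** The case for leaving this alone is that the abstract calls the analysis mainly descriptive, well-being is a secondary outcome, and the discussion says that change may not be due to the intervention and leaves effectiveness to a later randomized trial. No decision is tied to a P value. A full multiplicity scheme is also something a condensed article may leave to an analysis plan.

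Much of this stands, and it limits how serious the point is. It does not remove the contradiction. The article does not leave the level open; it fixes it twice, differently. The disclaimers concern causation without a control group, not an apparent change that is chance.

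Two stronger readings are tempting and are not supported.
- *False-positive improvements are close to certain.* Item scores are listed as end points, and the six questionnaires have 12 + 21 + 22 + 39 + 20 + 10 = 124 items, for which 1 − 0.95¹²⁴ = 99.8%. But the pre-post difference is defined on average questionnaire scores, and the analysis section lists constructs, not items. No section clearly plans 124 item tests. Items would also be correlated: at 0.3 to 0.7 the figure is 97% to 53%, and it counts both directions.
- *The correction was meant for well-being, so two well-being scores should become confirmatory.* The Sample Size section does not say so. The primary outcomes are also measured with exactly two questionnaires, MARS and UES-SF, which fits .05/2 at least as well.

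**Conclusion.** The point holds as an internal contradiction: .025 for design, .05 for each analysis, and no statement of which two comparisons the correction covers. Whichever two are meant, error across them doubles from 4.9% to 9.8% if they are independent. If the six questionnaire scores are the tests, it is about 26% under independence and 16% to 24% at the assumed correlations, with roughly half of that being false improvements. Adopting .025 for all six would still leave about 14% under independence, so aligning the number without naming the comparisons is not enough.

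The error rates need only the stated levels, the count of tests and the correlation assumption. The power figures rest on a standardized difference that the documents do not state. In a proof-of-concept study with well-being as a secondary outcome, this is a correction to make before results are labelled significant. It does not undermine the design.

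**What to change.** Replace the last sentence of the Quantitative Analysis section with wording to this effect: the two comparisons covered by the Bonferroni correction are [named by the sponsor] and are each tested at two-sided .025, as in the sample size calculation; all other scale scores are reported as estimates with 95% confidence intervals, labelled exploratory and without significance claims; item scores are reported descriptively. Name the same two comparisons in the Sample Size section and state there that the level is two-sided.

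The change is to wording only. It leaves 41 and 50 as they are, since .025 is the level that section already uses. One condition applies: if 41 was derived one-sided at a difference of 0.45, the two-sided test would need 50 completers, so the sponsor should confirm sidedness. The cost is that fewer results can be called significant.

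If all six questionnaires are to be tested formally, name one score for each, apply Holm across the six and restate the power. At an assumed difference of 0.5, power is about 65% at the strictest step with the planned sample.

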#### Qualitative Analysis

With regard to the analysis of the semistructured interviews, a text mining approach [38] will be used to extract the answers that appear repeatedly from the interviews that will be conducted with respect to the women’s experience of interacting with Maia and with respect to how they felt during the psychoeducational process.

### Ethical Considerations

This study was approved by the ethics committee of the APSS (15742; September 14, 2023). At the time of enrollment, all women who freely decide to take part in the study will be asked to sign an informed consent form after receiving a careful explanation of the study, its aims, the level of involvement required, and the duration of the research, as well as all ethical issues concerning confidentiality (the explanation of the study will be carried out partly by the midwives, but a video recorded by the research team with an explanation of the study, its purpose, and the woman’s level of involvement in simple and understandable words will also be available). The participants will be informed of the study's results through the app.

## Results

The psychoeducational course delivered through a virtual coach, Maia, integrated within the TreC Mamma app, is expected to have significant results regarding women’s satisfaction and involvement with the innovative digital solution.

Moreover, an increase in the levels of psychological well-being, QoL of the pregnant woman, emotional regulation, and positive affect is expected at the end the intervention compared to the beginning.

